## Background

Making use of opportunities for health promotion and disease prevention when people seek healthcare is critical to increasing the impact of healthcare on population health. Only 10–20% of what makes people healthy is attributable to the treatment of illness, while 30% has to do with individuals’ health behaviours [1]. According to recent reports of the World Health Organization, 22.3% of the world’s population use tobacco, 27.5% of the adult population do not meet the recommended level of physical activity, and 42.6% of the population are current consumers of alcohol [2,3,4]. In Alberta, 18% of the population smoke cigarettes, 28% engage in greater than low risk levels of alcohol drinking, and 70% do not get enough physical activity, as defined by the Canadian guidelines for a healthy lifestyle [5]. Tobacco consumption, alcohol misuse, and physical inactivity are leading modifiable risk factors for preventable chronic diseases (e.g., cancer, cardiovascular disease, respiratory diseases) and poor outcomes (e.g., complications and increased healthcare use or costs) [6,7,8,9,10,11,12,13,14,15]. According to the Canadian Population Attributable Riskfor Cancer study, in 2015, 28% of new cancer cases diagnosed in Canada were attributable to tobacco use, 5% to drinking alcohol, and 9% to physical inactivity [5]. Together, the three risk factors account for approximately 20% of total healthcare expenditures [15]. Importantly, these risk factors are modifiable by raising awareness and encouraging behaviour change; these negative impacts could be prevented or reduced by supporting patients’ health behaviour change [15,16,17]. Of the estimated 40% of cancers that are preventable, the greatest proportion are attributable to modifiable risk factors, including tobacco and alcohol use and insufficient physical activity [14].

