## Overview of the Program

### Description of intervention and settings

The IPiC-Health initiative is a three year project (January 2023-December 2025) that engages a variety of ambulatory and inpatient healthcare sites and providers in delivering SBIR for health promotion as a routine component of patient care. These sites provide care to patients with a variety of acute and chronic health issues, including rheumatological conditions, surgery, diabetes, pneumonia, asthma, cardiac diseases, trauma, and geriatrics. This initiative leverages the province-wide electronic (“Connect Care”) clinical information system to help integrate the SBIR actions and documentation sustainably into routine care. Screening involves using standardized screening questions to identify patients who use commercial tobacco, consume alcohol at levels that increase risk, or who participate in insufficient physical activity [28,29,30,31,32,33]. The brief intervention is a conversation that providers have with patients who have elevated risk on one or more of those modifiable risk factors. The brief conversation aims to educate patients about the health risks, identify patient readiness to consider a change in behaviour, and to encourage them to take action. Providers are then able to offer educational resources (e.g., a brochure containing QR codes/links to relevant websites) that provide behaviour change information and support. Providers can also refer patients to support services available in their community (e.g., Alberta Quits program for tobacco cessation) (Figure 1).

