### Research plans for evaluating implementation outcomes and process

*Study design and participants:* We use a quasi-experimental interrupted time-series design, covering a 6-month pre-implementation period and the last 12 months of the 15-month SBIR implementation period. The first three months of the implementation period are not used in analysis because we expect the quality of the SBIR intervention will mature over the first few months during which the clinical team learn to apply the practice.

*Definition and measurement of implementation outcomes*: Intervention reach (number) and patient population coverage (proportion) will be measured for each component of the SBIR intervention. Thus, the number of patients i) screened; ii) advised; and iii) referred in relation to each risk factor will be extracted each month from the Connect Care data. The denominator for the coverage (proportion) measures will be based on the total number of patients seen by a participating unit in the same month.

*Analysis:* For each outcome, we will calculate monthly summaries, aggregated across participating units. A Poisson regression model will be used to estimate the difference between the post-intervention observed rate and the “spontaneous” rate that would have occurred had SBIR been not implemented. The analysis will account for seasonality by decomposing the data in trend, seasonal, and random components, and then removing the seasonal component.

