**Implementation Phase (15 Months Intervention Period)**				

Implementation	Providers’ delivery of SBIR to patients: Reach or penetration of SBIR to patients; providers, intervention adherence	Proportion of patients being screened, advised, and referred for each risk factor	Connect Care documentation (electronic health records)	Connect Care data extraction, monthly time points for 15 months

Implementation	Acceptability, appropriateness, and feasibility of SBIR implementation	Proportion of providers being agreed or strongly agreed that SBIR implementation is acceptable, appropriate, and feasible in clinical settings	Primary data collection from providers who implemented SBIR	Survey using a validated tool at six and 12 months of implementation initiated

Implementation	Adherence or adaptation to SBIR implementation and real-world practice change challenges/barriers	Whether providers achieve the goal of screening all patients for the three risk factors and offering brief advice and referral to all eligible patients and if not, why; whether any adaptations were made in implementation, what they were, and why adaptions were made.	Primary data collection from providers who implemented SBIR	Regular conversations/interactions during regular meetings between clinical and research teams using a standardized template.

Implementation	Factors influencing implementation	Unit- and organization-related barriers/facilitators or contextual factors to SBIR implementation	Primary data collection from clinical and administrative leadership (e.g., nurses, unit managers, implementation facilitators)	In-depth interviews at three and nine months after implementation initiated

Patients follow ups: Patients’ experience and perspective	Patient’s knowledge and experience (intervention patient groups)	knowledge about the impacts of the risk factors on health risks and the available services/programs for behavior change; acceptability, perceived stigma, and any challenges with SBIR process or related materials; barriers/facilitators to risk factor-related behavior change.	Primary data collection from patients	Follow up in-depth telephone interviews with a small sample at one months of index hospitalization discharge/visit (recruitment or intervention receive time).

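### Advice and referral coverage, divided by all patients seen, measures population reach and not the provider adherence that Table 1 also assigns to it

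*Protocol article*

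**What the plan says.** Under Research plans for evaluating implementation outcomes and process, the counts to be taken from Connect Care are listed: "the number of patients i) screened; ii) advised; and iii) referred in relation to each risk factor will be extracted each month". A single denominator follows: "The denominator for the coverage (proportion) measures will be based on the total number of patients seen by a participating unit" in that month. No count of patients found at increased risk is listed, and the article gives no at-risk or eligible-patient denominator anywhere.

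The Implementation Phase part of Table 1 lists the proportions screened, advised and referred as the measure of "Reach or penetration of SBIR to patients; providers, intervention adherence". A separate row of that table states "the goal of screening all patients for the three risk factors and offering brief advice and referral to all eligible patients" and asks whether providers achieve it. The information for that row comes from conversations at regular meetings, recorded on a standardized template.

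The section Description of intervention and settings says who should receive advice: "The brief intervention is a conversation that providers have with patients who have elevated risk on one or more of those modifiable risk factors". The effectiveness section has the same sequence: intervention patients first screen at increased risk and then receive brief intervention and referral support.

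**The concern.** Screening and the two later steps have different target groups. All patients seen is the right base for screening. For advice and referral, that base includes patients for whom neither step is intended, so the proportion depends on how common the risk factor is and how complete screening was, as well as on what providers did.

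The label adherence in Table 1 is what makes this matter. A reader of the results would naturally take a low advice proportion as poor adherence, when it could equally come from a low prevalence or from incomplete screening. The distinction is a live one: Expected Results and Applicability lists high screening and low brief intervention among the learnings so far, and whether advice is low relative to need is a question that the planned proportion does not answer.

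**Working it through.** The article states no coverage figure or target percentage, so there is nothing to reproduce. The check is on what the defined measure can show.

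**Inputs**
- Denominator: all patients seen by the unit in the month (implementation outcomes section).
- Target of advice and referral: patients at increased risk (Description of intervention and settings; Table 1).
- Prevalence, Alberta population: "18% of the population smoke cigarettes, 28% engage in greater than low risk levels of alcohol drinking, and 70% do not get enough physical activity" (Background).
- Prevalence among hospital patients: 43% to 90%, not split by risk factor (Background).
- Assumptions: advice on a factor goes only to patients screened and found at risk on it; prevalence is the same in screened and unscreened patients. Prevalence at the participating units is not given, so the percentages below are illustrations.

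**Formula**

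Coverage of advice = screening share × prevalence × delivery to at-risk patients identified. The same form holds for referral.

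**Step 1. Ceiling.** With screening and delivery both at 100%, coverage equals prevalence: 18%, 28% and 70% on the Alberta figures, or 43% to 90% on the hospital range.

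**Step 2. Good delivery.** With full screening and 90% delivery:

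| Prevalence used | Calculation | Coverage reported |
|---|---|---|
| Tobacco, 18% | 0.90 × 0.18 | 16.2% |
| Alcohol, 28% | 0.90 × 0.28 | 25.2% |
| Inactivity, 70% | 0.90 × 0.70 | 63.0% |
| Hospital range, low, 43% | 0.90 × 0.43 | 38.7% |
| Hospital range, high, 90% | 0.90 × 0.90 | 81.0% |

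**Step 3. One value, different delivery.** Suppose advice coverage of 14% with everyone screened. Delivery to at-risk patients is then 0.14 / 0.18 = 78% for tobacco, 0.14 / 0.28 = 50% for alcohol and 0.14 / 0.70 = 20% for inactivity.

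**Step 4. Screening or advice?** For alcohol, 14% arises from full screening with half of at-risk patients advised (1.0 × 0.28 × 0.5) and also from half screened with all at-risk patients advised (0.5 × 0.28 × 1.0).

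**Step 5. The time series.** If delivery rises from 10% to 50% with full screening and stable prevalence, the ratio is (0.18 × 0.5) / (0.18 × 0.1) = 5.0, and also 5.0 at a prevalence of 70%. Prevalence cancels, so the planned contrast is sound in that case. If tobacco prevalence moved from 18% to 22% with delivery unchanged at 50%, the ratio would be (0.22 × 0.5) / (0.18 × 0.5) = 1.22. That shift is hypothetical.

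**The case against.** The strongest defence is that the denominator suits the named outcome and the planned analysis. The article calls the outcome population coverage and puts it into an interrupted time series, which needs a base that exists in both periods and is not moved by the intervention. Patients screened at increased risk is not such a base: the intervention itself drives screening, and recruited control patients are screened on paper by research coordinators, not by the clinical team. This stands, and the stated denominator should stay for that analysis.

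Some of the information is also already recoverable. With counts screened and advised both extracted, advised over screened can be formed. That removes the screening share, but the result is still prevalence × delivery, so the comparison in Step 3 is unchanged.

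It may be said that a condensed article leaves supplementary proportions to the full protocol. That would answer an omission. Here the article itself fixes the denominator and assigns adherence to the resulting proportions.

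Three stronger readings are tempting, and the documents do not support them:
- A reader might infer that attainment of the goal goes unassessed. Table 1 does plan an assessment; it rests on meeting conversations and not on a count.
- A reader might infer that the early finding of low brief intervention is an artefact of this denominator. The article does not say how that finding was computed, and it reports separately that brief interventions are often undocumented.
- A reader might infer that planned comparisons across risk factors or units are invalid. The implementation analysis plans no test across factors, and it aggregates the monthly summaries across units.

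**Conclusion.** The point holds in a limited form. The advice and referral proportions are usable as population reach, and in the before/after series if case mix is stable. As defined, they are not a measure of provider adherence, because they are capped by screening share × prevalence. On the assumptions listed, 90% delivery would read as anything from 16% to 81%, depending on the risk factor and on which of the article's prevalence figures applies. The ceiling follows from the definitions; the particular percentages depend on full screening and on prevalences that may not hold at these units. No effectiveness estimate is affected.

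**What to change.** Keep all patients seen as the denominator for screening and for the interrupted time series. For the implementation period, add the monthly number screened at increased risk on each factor to the Connect Care extract. Report advised / screened at increased risk and referred / screened at increased risk as the adherence measures, and label the existing advice and referral proportions as reach only.

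The cost is a sentence in the outcome definition and one more monthly count per risk factor. That the count can be extracted is inferred from the article's statement that Connect Care holds the screening tools and risk algorithms; it is not stated and should be confirmed. Analysis awaits complete data, so the change can still be made.

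There are limits. The new denominator exists only where screening was done, so it must be read beside the screening proportion. It does not repair the under-documentation of brief interventions. The article also lets providers judge suitability and patients decline, so a value below 100% would not by itself show poor adherence.

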**Pre-implementation Phase (6 Months Control Period)**				

Baseline, for comparison of SBIR (Screening Brief Intervention, and Referral) effectiveness	Tobacco consumption, alcohol intake, and physical activity levels	Proportion of patients with tobacco consumption, alcohol misuse, and insufficient physical activity levels	Primary data collection from comparison patient group	Paper-based self-administered questionnaire

Pre-implementation (baseline) delivery of SBIR elements by clinical team members.	Providers’ baseline delivery of SBIR elements to patients	Proportion of patients being screened, advised, and referred for each risk factor	Connect Care documentation (electronic health records)	Connect Care data extraction, monthly time points for six months

Baseline	SBIR implementation readiness	Leadership engagement/support, resources for SBIR, providers’ motivation	Primary data collection from providers and organizational leaders	Self-administered questionnaire, interview, and observation

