## Expected Results and Applicability

Thus far 4 inpatient units and 4 ambulatory clinics in Calgary and Edmonton cities in Alberta have participated in this project. Among those, 1 inpatient unit and 4 ambulatory clinics have completed the 6 months control period and started the implementation of SBIR, and remaining units/clinics are in the 6 months control phase. We have recruited a total of 2015 patients as control research participants (i.e., medium or high-risk level on any of the three risk factors). Of those, 1000 have completed 6 months follow-up calls. A total of 447 patients have received SBIR support from the participating units/clinics, with 175 patients being intervention research participants (i.e., consented for follow up survey). Among those intervention research participants, 48 have completed 1 month follow up survey calls, 75 have completed 6 months follow up calls, and 23 have participated in in-depth qualitative interviews. Approximately 50% of patients are responding to follow-up efforts.

The research participants recruitment and data collection activities are undergoing and key learnings to date are as follows.

High screening uptake: Providers are consistently screening and documenting for the risk factors.Low brief intervention rates: Offering brief advice or engaging patients in conversations about behavior change remains relatively low.Low documentation of brief intervention: When brief interventions are provided, they are often not documented in the Connect Care system.Referral gaps: Referral pathways—particularly for physical activity and alcohol use—are unclear, and referral functionalities for these risk factors are not currently integrated into the Connect Care system.Facilitators of implementation: Implementation is supported by clinical champions, embedded project staff at implementation sites, and ongoing rapid assessment and feedback.Participant eligibility challenges: Many patients are ineligible for the intervention or study participation due to critical health conditions particularly in some high acute care settings. This indicates that careful consideration of the setting and patient acute is important when deciding whether to implement SBIR.Improved recruitment: Using both in-person and phone-call recruitment strategies has led to an increase in participant numbers.

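### Removing seasonality by decomposing a short monthly series pooled across units lets part of the SBIR effect pass as season; a joint unit-by-month model on the same data avoids this

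*Protocol article*

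**What the plan says.** Under *Research plans for evaluating implementation outcomes and process*, the article sets an interrupted time series "covering a 6-month pre-implementation period and the last 12 months of the 15-month SBIR implementation period". It adds that "The first three months of the implementation period are not used in analysis", to let clinical teams learn the practice. For each outcome, "we will calculate monthly summaries, aggregated across participating units". The estimand is a contrast with the rate expected had SBIR not been introduced: "A Poisson regression model will be used to estimate the difference between the post-intervention observed rate and the" rate expected without SBIR. Seasonality is handled as a separate operation: "The analysis will account for seasonality by decomposing the data in trend, seasonal, and random components, and then removing the seasonal component".

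Table 1 gives the length of the data. Before implementation it lists "Connect Care data extraction, monthly time points for six months", and during implementation "Connect Care data extraction, monthly time points for 15 months". No longer historical series, external control series or other seasonal model is described. The coverage denominator is the number of patients seen by a unit in the month, so unit-level monthly data are already part of the plan.

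*Expected Results and Applicability* shows that units start at different times. It reports 4 inpatient units and 4 ambulatory clinics so far: "Among those, 1 inpatient unit and 4 ambulatory clinics have completed the 6 months control period and started the implementation of SBIR", while the remaining units are still in their control phase.

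**The concern.** A trend/season/remainder decomposition learns the season from repeated calendar months under otherwise comparable conditions. Here few calendar months repeat, and in a series counted from each unit's start every repeat has SBIR off the first time and on the second. The decomposition does not know when SBIR began, so it can assign part of the change to season. Removing that season then removes or reshapes part of the effect.

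Pooling across units adds a second difficulty. The article does not say whether months are counted from each unit's start or by calendar. The first choice mixes calendar seasons in each point. The second mixes units before and after implementation in each point.

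The reach and coverage results are at stake, that is, the share of patients screened, advised and referred. The article expects uptake to grow during the intervention period, so the analysis must be able to tell step, slope and season apart.

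**Working it through.** The article states no number of time points, so there is no figure to reproduce. It follows from the stated windows. An annual season (period 12) is assumed, since no period is given.

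**Length.** Analysed: 6 + (15 − 3) = 18 months, and 18/12 = 1.5 cycles. Extracted: 6 + 15 = 21 months, and 21/12 = 1.75 cycles. Classical decomposition needs 2 × 12 = 24. A standard routine stops at 18 and at 21 points and runs at 24.

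**A. Months counted from each unit's start (1–6 and 10–21)**

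- *Repeats.* The 12 later months contain each calendar month once, and the 6 earlier months repeat six of them. Six calendar months are therefore seen only under SBIR, and none is seen twice in the same phase.
- *Aliasing.* Let P = 1 from month 10 on and take t − 12P. In months 1–6 it equals 1 to 6, and in months 13–18 it again equals 1 to 6. In months 10–12 it equals −2, −1, 0, and in months 19–21 it equals 7, 8, 9. It depends on calendar month alone, so month effects reproduce it exactly. A trend of 1 per month cannot be told from a step of 12. The design with intercept, trend, step and 11 month indicators has rank 13 of 14; with a slope change, 14 of 15.
- *STL.* It runs at 18 points, with the three-month gap closed up. Given a pure step of 1.00, no season and no noise, the post-minus-pre difference after removing its season is 0.73. On all 21 points the same difference comes back as 1.00, but STL still draws a season of up to ±0.46 where there is none, so the shape of the series is distorted.
- *One harmonic pair.* It is estimable. With a step and slope change, the standard error of the step rises from 1.70 to 2.92 times the monthly residual SD.

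**B. Calendar months**

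Assume 5 units start together and 3 start 6 months later, with the three learning months dropped.

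- *Span.* 21 + 6 = 27 months, all with data, so classical decomposition runs.
- *Identifiability.* A pooled model with 11 month indicators, trend and the fraction of units past the switch has rank 14 of 14, with an effect SE of 0.95 times the residual SD.
- *Interruption.* The pooled exposure is 0 up to month 9, 5/8 = 0.625 in months 10–12 and 1 from month 13. There is no single change point.
- *Decomposing first.* Given a pure effect of 1.00 with no season, classical decomposition returns a season running from about −0.24 to +0.25. A simple contrast on the adjusted series gives 0.95. With an assumed 3-month offset it gives 0.82. Keeping the learning months and switching at month 7, with a 6-month offset, gives 1.02.
- *Longer offset.* At 9 months, only 27 of the 30 calendar months have any data.

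**C. Unit-by-month model (8 × 18 = 144 rows)**

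The columns are unit effects, calendar trend, step and post-implementation slope, plus season.

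| Starts (assumed) | 11 month effects | One harmonic pair |
|---|---|---|
| All together | rank 21 of 22 | 13 of 13 |
| Two waves, 6 months apart | 22 of 22 | 13 of 13 |
| Two waves, 12 months apart | 21 of 22 | 13 of 13 |
| One month apart | 22 of 22 | 13 of 13 |

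The rank results are properties of the design and apply equally to a log-linear Poisson model. The standard errors use a linear predictor and are indicative only.

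**The case against.** The strongest reply is that 18 points is one reading. Season is a calendar matter, so calendar pooling is natural, and the article implies a longer calendar series. It reports 75 intervention participants with completed 6-month calls, so the earliest unit began its 6-month control phase about 12 or more months ago. Units still in that phase began at most 6 months ago. The stagger is therefore about 6 months or more, and the span at least 21 + 6 = 27 months. This stands. A reader might infer that the analysis cannot be computed, or that the SBIR effect is not identified at all. The documents do not support that: the failure of classical decomposition and the aliasing belong to the unit-start axis. STL and a harmonic term run even there, and the article names no routine. What remains is that decomposing first distorts the result on either axis.

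Two further inferences also go too far. One is that Poisson regression becomes invalid because deseasonalised counts are not integers; Poisson estimating equations need a correct mean, and an estimated scale handles the rest. The other is that the comparison rests on extrapolating a straight line through six points; the article does not say that the counterfactual is formed this way.

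It is also fair that the practical bias is not shown. Dividing by patients seen removes much of the seasonal change in volume from coverage, though not from reach counts. A large rise in screening could dwarf any season. Against that, the article reports that brief advice remains fairly low, is often undocumented, and has referral gaps, so changes there may be modest.

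Finally, some detail may sit in a separate analysis plan. But the article itself fixes the windows, the pooling and the seasonal method, and a plan that follows them inherits the problem.

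**Conclusion.** The concern holds in limited form. Decomposing the pooled series and removing its seasonal part is a poor way to adjust for season in this design, whichever way months are counted. Counted from each unit's start, there are 1.5 cycles, trend and step are aliased under month effects (13 of 14), and STL at 18 points returns 0.73 for a true 1.00. By calendar, the effect can be identified, but the pooled series has no single interruption, and decomposing it first yields a spurious season of about ±0.24 under the assumed waves. The net effect on the estimate there ranges from slight to moderate (1.02, 0.95 and 0.82 in the cases tried). On both axes, standard errors from a model fitted after the filter leave out the uncertainty of the season removed.

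These sizes rest on an annual period, noise-free series and assumed start offsets. The real bias depends on baseline rates that the article does not give; it may be small for screening and larger for advice and referral. The effectiveness analysis and its sample size are not touched.

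**What to change.** Replace the decomposition and the pooling with one model fitted to the monthly data by unit:

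- quasi-Poisson with log(patients seen) as offset, or binomial with patients seen as denominator;
- unit effects, a common calendar trend, and a low-dimensional season (one harmonic pair);
- a step and a post-implementation slope, both starting at each unit's own implementation month 4, so that the expected growth in uptake is modelled and not forced into a step;
- standard errors robust to overdispersion and autocorrelation, with a small-cluster correction.

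State that the time axis is calendar time. Before fitting, check identifiability against the actual start dates: full month-of-year effects are not identified if units start together or in waves exactly 12 months apart, which is why the harmonic pair is the safer default.

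The cost is a change of analysis wording, since the monthly extracts and unit denominators are already planned and the article says analysis awaits complete data. The price in precision is wider standard errors, because only 8 units have joined so far and the seasonal uncertainty is now counted.
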